#### Parenting attitudes

To assess parenting attitudes related to expectations, empathy, and discipline, the Adult Adolescent Parenting Inventory, Version 2.0 (AAPI-2) will be used [46]. The AAPI-2 comprises 40 items and five constructs: inappropriate expectations of children, parental lack of empathy towards children’s needs, strong parental belief in the use of corporal punishment, reversing parent-child family roles, and oppressing children’s power and independence.

#### Self-efficacy and satisfaction as a parent

To assess self-efficacy and satisfaction as a parent, the Being a Parent Scale will be used [47]. This tool has 16 items and requires parents to rate whether they feel each item applies to them, using a 6-point Likert scale ranging from 1 (strongly agree) to 6 (strongly disagree).

#### Quality and quantity of stimulation available to the child

To assess the quality and quantity of stimulation available to the child, the Home Observation for Measurement of the Environment (HOME) Inventory, a 45-item questionnaire, will be used [48]. This tool contains six domains (responsivity, acceptance, organization, learning materials, involvement, and variety) and is used by a trained assessor to indicate whether a behaviour is observed or reported by the parent during the home visit.

#### Maternal depression

To assess maternal depression, the Center for Epidemiological Studies Depression Scale (CES-D) [49] will be used. The CES-D contains 20 items and requires individuals to rate how often they experienced symptoms of depression over the past week.

#### Maternal anxiety

To assess anxiety symptoms, the Beck Anxiety Inventory (BAI) will be used [50]. The BAI comprises 21 items and requires individuals to rate how often they experienced symptoms of anxiety in the past week, using a 4-point scale ranging from “Not at all” to “Severely - I could barely stand it”. A total score is obtained by summing all of the items and can be categorized by low anxiety, moderate anxiety, or potentially concerning levels of anxiety.

#### Maternal adverse childhood experiences

To assess maternal ACEs, mothers will retrospectively report on their ACEs prior to 18 years of age using a 10-item questionnaire with “yes/no” questions pertaining to abuse, neglect, and household dysfunction [51].

### Data collection

Informed by our previous longitudinal, multi-informant, and multi-site research with substance-involved mothers, data for the present study will be collected at three time points: pre-intervention, 12-, and 24-months after engagement in services. This longitudinal design will assess whether infant mental health improves and is sustained through a two-year period. The length of engagement in each of the intervention programs varies (mean length is 18 months with a range of 4 to 71 months) [52]. As such, some mothers will remain in the program for the duration of the study while others will not. The evaluation of primary and secondary outcomes will be similar for BTC and MWCHC, the only differences being that the HOME Inventory will not be applied at MWCHC. Data will be collected by the clinicians providing services onsite and by one CBR embedded at each site. The mothers’ clinical files will be reviewed by the CBRs to gather demographic data, addiction information, trauma and psychosocial risk information, treatments accessed, and treatment duration via retrospective file review. The CBRs will receive training on how to administer the MBQS and will be responsible for the in vivo observations and coding of the mother-child relationships. Participants who are no longer receiving services will be offered the opportunity to return to the intervention program for subsequent data collections, to complete the questionnaires over the phone, or to meet at a neutral location. Mothers will receive compensation for their time in the form of gift certificates to grocery stores at each time point.

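### The HOME is described as scored during a home visit, but the follow-up routes offered to mothers who have left services omit the home, so within-BTC change in HOME would be selected on length of stay

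*Protocol article*

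**What the plan says.** The Secondary outcome measures section, under the heading on quality and quantity of stimulation, states that the HOME "is used by a trained assessor to indicate whether a behaviour is observed or reported by the parent during the home visit". Both ways of filling in an item, observation and parent report, are placed within that visit.

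Data collection sets the assessments at "pre-intervention, 12-, and 24-months after engagement in services". It gives the length of engagement ("mean length is 18 months with a range of 4 to 71 months") and accepts that "some mothers will remain in the program for the duration of the study while others will not". For leavers it lists three options: "to return to the intervention program for subsequent data collections, to complete the questionnaires over the phone, or to meet at a neutral location". It also says that "the HOME Inventory will not be applied at MWCHC", so HOME data come from BTC alone.

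Research question 1b (Objective) lists environment scores among the outcomes whose change to 24 months is of interest. Statistical analysis handles secondary outcomes in much the same way as the primary ones, with linear mixed models, and notes that such models can use participants whose data are incomplete.

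**The concern.** The HOME is the only instrument in the article that is tied to the family's home. The questionnaires can be done by phone, and the maternal behaviour measure needs only a ten-minute live interaction, which a programme room or neutral site can host. The list of routes for leavers therefore serves every measure except this one.

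If sites follow the list, whether a mother has a 12- or 24-month HOME score depends on whether she is still in the programme. Time in treatment is the exposure in research question 2 and is expected to relate to outcome. A rise or fall in HOME within BTC could then partly reflect who stayed. The covariates named as examples in Statistical analysis (maternal age, socioeconomic status, maternal ACEs) do not include time in treatment, so the model as described does not deal with this.

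The stake is limited to within-BTC change in HOME. HOME data not collected at the time of the visit cannot be recovered later.

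**Working it through.** **Step 1. The two statements side by side.**

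| Needed for HOME (outcome description) | Offered to mothers who have left (Data collection) |
|---|---|
| Trained assessor, at a home visit | Programme site: not the home |
| Item observed at that visit | Phone, for questionnaires: nothing can be observed |
| Or item reported by the parent at that visit | Neutral location: not the home |

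No other way of scoring the HOME is described.

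**Step 2. The plan's own figures.** The article states no expected HOME coverage, so there is none to reproduce. Its sample size concerns ASQ-3 change only. With 34 per group, d = 0.70 and two-sided alpha 0.05, the noncentral t gives 81.2% power against the stated 81.1%, and 34/0.70 = 48.6, rounded up to 49 per group. No HOME data enter that calculation.

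**Step 3. How many have left, without assuming a distribution.** Inputs from Data collection: mean stay 18 months, minimum 4. Let T be length of stay. Markov's inequality applied to T − 4 gives

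P(T ≥ t) ≤ (18 − 4)/(t − 4).

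- At 24 months: 14/20 = 0.70, so at least 30% have left.
- At 12 months: 14/8 = 1.75, which exceeds 1. The mean and minimum alone guarantee nothing at 12 months.
- If stays shorter than 4 months can occur, the 24-month bound becomes 18/24 = 0.75, so at least 25% have left.

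**Step 4. Illustration under assumed shapes.** All have mean 18 months. The shapes and SDs are assumptions; the article gives neither.

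- Exponential: S(t) = exp(−t/18).
- Shifted exponential: S(t) = exp(−(t − 4)/14).
- Lognormal: σ² = ln(1 + (SD/18)²), μ = ln 18 − σ²/2.
- Gamma: shape k = (18/SD)², scale 18/k.

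| Assumed distribution | Still engaged at 12 months | Still engaged at 24 months |
|---|---|---|
| Exponential | 51% | 26% |
| Shifted exponential | 56% | 24% |
| Lognormal, SD 8 | 77% | 19% |
| Lognormal, SD 10 | 70% | 21% |
| Lognormal, SD 15 | 58% | 22% |
| Lognormal, SD 18 | 53% | 22% |
| Gamma, SD 8 | 76% | 20% |
| Gamma, SD 10 | 69% | 23% |
| Gamma, SD 15 | 57% | 26% |

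Across these, 51% to 77% are still engaged at 12 months and 19% to 26% at 24 months, so about 74% to 81% have left by 24 months. Of 50 BTC mothers (Participants), that leaves about 26 to 39 engaged at 12 months and 9 to 13 at 24 months. I have not multiplied by the roughly 30% study attrition, because mothers lost to the study may largely be those who left services.

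**The case against.** The best case against the point has five parts.

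*The text does not forbid home visits.* Leavers are offered three routes, and nothing says these are the only contacts. Baseline is taken before any services are received (Recruitment), so a baseline HOME visit cannot depend on BTC's home-visitation service, and later ones need not either. A condensed article may also leave such logistics to the full protocol. This stands against the inference that the HOME cannot be given to leavers. What remains is that the article does state the routes, and its list omits the one setting the instrument is described as needing.

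*The specified HOME analysis already cannot be run.* Question 1b compares the two programmes, and the comparison site has no HOME data. That is a separate and larger problem. It confines this point to within-BTC change, which the article does not set out as an analysis of its own.

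*Coverage figures.* A reader might infer that every mother has a baseline HOME and only about 11 of 50 have one at 24 months. The documents support neither. Pregnant women may enrol, and full baseline coverage is not stated. The 24-month figure needs an assumed distribution and no home visit to any leaver.

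*Missing data.* A reader might infer that the missingness cannot be ignorable. That does not follow: treatment duration is recorded by file review and can be conditioned on, and the named covariates are only examples.

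*The model.* A mixed model does not simply set all mothers at baseline against stayers at 24 months; it uses each mother's available measurements. Its estimate of late change would still rest on stayers' follow-up and on a missing-at-random assumption.

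**Conclusion.** The point holds in a limited form. The description of the HOME and the list of follow-up routes do not fit together, and the list, followed as written, would tend to restrict 12- and 24-month HOME scores to BTC mothers still in the programme. Within-BTC change in HOME would then be selected on length of stay.

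The firm figure is that at least 30% of mothers would have left by 24 months, given the stated mean and minimum and applying them to BTC. The larger share, about three quarters to four fifths, is an illustration under assumed skewed distributions.

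HOME is a secondary measure, is collected at one site and is not among the listed mediators. The primary outcomes, the main comparison between programmes and the sample size are unaffected. The point is worth acting on because the edit is small.

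**What to change.** - In Data collection, add the family's home, where the mother agrees, to the locations offered at 12 and 24 months to BTC mothers who have left services.
- State that the HOME is not scored from phone or neutral-site contact. By the same reasoning, a visit to the programme site does not replace the home visit.
- Report HOME coverage at each time point by engagement status.
- Include the recorded treatment duration in any model of within-BTC change in HOME.
- If home visits after leaving are not feasible, say so, report HOME descriptively, and do not interpret its 24-month change.

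The cost is a few lines of protocol text and some travel for an assessor already trained on the instrument. Some mothers will decline a home visit, so coverage will improve but need not be complete. The fallback costs nothing to run but gives up the 24-month HOME result. The wording should be settled before follow-up visits take place.

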### Data management

The CBRs will be responsible for collecting the paper questionnaires and entering the data electronically on the BTC and MWCHC servers. These servers will be used to store the research data as they are secure and regularly used to provide confidential and secure clinical services. All electronic files will be password protected and the paper copies of the questionnaires will be stored in a locked filing cabinet at BTC and MWCHC. Once data collection is complete, the data will be shared with the research team and stored at the University of Ottawa for the analysis period. The data will remain on the University of Ottawa secure servers in a locked laboratory facility on the university’s campus. All computers in the laboratory are kept behind locked doors and have secure login requirements. During the storage period, investigators on the research team will have access to the data. As well, research assistants working within the labs of the investigators will have access to data to assist with analyses and contribute to any research dissemination activities. The data and research documents will be retained for 10 years after the completion of the study.

### Statistical analysis

All data analyses will be conducted in SAS and Mplus. For research question 1a, linear mixed models will be used to model the change in each of the primary outcomes from baseline to 24-months post-engagement for the BTC and MWCHC groups, controlling for demographic variables that potentially differ at baseline (e.g., maternal age, socioeconomic status, maternal ACEs). Slopes of the two groups will be compared using an interaction term. Linear mixed models can accommodate participants with missing observations [20]. For research question 1b, we will analyze secondary outcomes with a similar approach. For research question 1c, we will conduct regression analyses to predict which risk and protective factors identified at baseline predict change in the primary outcome for the BTC group.

For research question 2, we will conduct a series of mediation (indirect effects) and moderator analyses (interaction effects) for the BTC group, with time in treatment as the independent variable and infant mental health outcomes at 24 months as the dependent variable. Mediator (i.e., maternal behaviour, parenting attitudes, and maternal stress) and moderator (i.e., psychosocial risk) variables at 12 months will be used in all analyses.

For research question 3, we will adopt international guidelines for SROI [53]. SROI comprises a structured framework to identify, measure, and value the wider societal impacts of an intervention. [53] To support this work, a four-step approach will be adopted: first, using comparative effectiveness evidence from research question 1, information on key mechanisms of change from research question 2, and in partnership with the study’s Steering Committee, we will develop a theory of change to model BTC program inputs, outputs, outcomes, and potential lifetime health and non-health impacts for children engaged in the intervention. Using Microsoft Excel, we will develop a decision analytic model (e.g., decision tree) to link the program theory of change to an economic framework for analysis. We will then undertake a scoping review of the published and grey literature to identify studies and potential data sources that can be used to estimate the monetary value associated with multi-sector program outcomes and impacts (e.g., reduced adverse health and mental health outcomes, improved academic outcomes, and improved economic productivity). Next, we will estimate the costs of implementation of the BTC program based upon the resources required for implementation, as outlined in our theory of change (inputs). Finally, we will combine the evidence on intervention program outcomes and impacts (benefits) and cost of implementation (costs) to yield a benefit-cost ratio, which will provide an estimate of the broader socio-economic returns to society for every dollar invested in BTC. Where there is uncertainty in estimates (e.g., the monetary value that can be attributed to a specific outcome), we will conduct sensitivity and threshold analyses to determine the impact of varying these estimates over a range of acceptable values on the overall SROI calculation. All costs and benefits that are incurred beyond one year will be discounted at an annual rate of 1.5%, in line with Canadian guidelines [21], to estimate the net present value of the SROI [54].

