## Methods

### Design

This intervention study is designed as a non-randomized, non-equivalent, comparison study with two equally allocated parallel groups: the BTC intervention group and the MWCHC intervention group. Given that the two intervention programs serve a similar demographic of women, researchers will compare the BTC and MWCHC groups to establish the comparative effectiveness and mechanisms of change of the additional infant mental health component of BTC. The study has been approved by the University of Ottawa Research Ethics Board (REB # H-02-23-8940) and is registered with ClinicalTrials.gov (NCT05768815). All research is performed in accordance with relevant guidelines and regulations. This protocol paper adheres to the SPIRIT guidelines (see Additional file 1).

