### Sample size and power calculations

The study is powered to detect a between-group effect size of Cohen’s d = 0.70 in the primary outcome (change in ASQ-3 between baseline to 24-month post-engagement) for research question 1a. This estimated effect size is conservative compared to the effect size reported in a similar study [55]. Using G*Power v3.1.9.7 [24], assuming a two-sided two-sample t-test with un-pooled variance, we estimate that *N* = 98 participants will be required (*n* = 49 per group). Assuming ~ 30% participant attrition [25], a sample size of *N* = 68 participants with complete data (*n* = 34 per group) achieves 81.1% power (a = 0.05) to detect between-group differences in the primary outcome. Thus, *n* = 50 per group will be sufficient.

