## Discussion

This study is the first to examine the effectiveness of infant mental health components of a mother-child relationship-focused intervention program on infant mental health outcomes as compared to a mother-focused program. It aims to establish the comparative effectiveness and mechanisms of change of the infant mental health components of BTC, as well as estimate the long-term SROI of the integrated BTC approach. The involvement of MWCHC participants as a control group is a considerable strength of the study, thus making it possible to attribute changes in infant mental health outcomes to the enhanced BTC intervention. Although non-randomized studies suffer from an inherent selection bias, randomization is not possible due to feasibility and ethical reasons. Analytic approaches will be used to minimize any baseline differences between the BTC and MWCHC groups.

It is important to note that while the MWCHC program does not provide the same level of direct intervention with children as the BTC program, children do receive healthcare and well-baby visits. As well, MWCHC mothers receive basic parenting supports and mental health and addiction services that indirectly benefit their children. Their participation in this study will allow them to receive a summary report after every time point, containing an overview of their results as well as a developmental report for their child that they would not have otherwise received. Among other benefits for MWCHC participants, the implementation of the clinical measures will allow for better screening and referral and will increase evidence-based knowledge provided to clinicians. The introduction and embedment of a CBR will also enhance the capacity for research at each site, thus increasing the quality of regular clinical services being offered.

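### Time-fixed baseline covariates entered as main effects do not adjust the slope contrast that tests the programme effect, so measured confounding of change would stay in research questions 1a and 1b

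*Protocol article*

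**What the plan says.** The Design section describes a "non-randomized, non-equivalent, comparison study with two equally allocated parallel groups". Outcomes are measured at three points: "pre-intervention, 12-, and 24-months after engagement in services".

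For research question 1a, the Statistical analysis section says that "linear mixed models will be used to model the change in each of the primary outcomes from baseline to 24-months post-engagement", "controlling for demographic variables that potentially differ at baseline (e.g., maternal age, socioeconomic status, maternal ACEs"). It then says: "Slopes of the two groups will be compared using an interaction term". The secondary outcomes follow: "For research question 1b, we will analyze secondary outcomes with a similar approach".

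The sample-size section powers the study for a "between-group effect size of Cohen’s d = 0.70 in the primary outcome (change in ASQ-3 between baseline to 24-month post-engagement"), so the target is a difference in change.

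The Discussion concedes selection bias and adds: "Analytic approaches will be used to minimize any baseline differences between the BTC and MWCHC groups". It names no approach. The same paragraph holds that having the comparison site allows changes in child outcomes to be attributed to BTC.

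**The concern.** The estimand is a difference in rate of change, while the only adjustment named concretely is control for variables that do not vary over time. Entered in the ordinary way, such variables explain why some children score higher or lower throughout. They do not explain why some children improve faster, and that is where confounding of a slope contrast arises.

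The article itself makes such confounding plausible. Research question 1c asks which baseline risk and protective factors predict change in the primary outcome, so the authors treat baseline factors as possible drivers of change. The sites also differ in structure: they are in different provinces, and Table 1 lists a plan to parent as a feature of BTC but not of MWCHC.

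The programme contrast carries the causal claim in the Discussion and supplies the effectiveness evidence for the social return on investment. A bias in it would pass into both.

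**Working it through.** **The plan's own figure.** With d = 0.70, 34 per group and two-sided alpha 0.05, the noncentrality is 0.70 × √(34/2) = 2.89 on 66 degrees of freedom, giving 81.2% power against the stated 81.1%. Inflating for attrition, 34/(1 − 0.30) = 48.6, so 49 per group and N = 98, as stated. The sample-size figures are not in dispute.

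**Why main effects drop out.** Take complete data at 0, 12 and 24 months. Centred time is −12, 0, +12, so each child's fitted slope is

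b = (y24 − y0)/24,

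and the group-by-time estimate is mean b at BTC minus mean b at MWCHC. A main effect γx adds the same amount to y0 and y24 and cancels from b. If x also changes the course by δ per unit of time, then

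estimate = programme effect + δ × (mean x at BTC − mean x at MWCHC),

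and the second term stays whether or not x is in the model as a main effect. An x-by-time term estimates δ and removes it.

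**Size in SD of 24-month change.** For one covariate, bias = (between-site gap in SD) × (correlation with change). Neither input is in the article; both are assumed.

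- No correlation with change: bias 0.
- Gap 0.5, correlation 0.3: 0.5 × 0.3 = 0.15, which is 0.15/0.70 = 21% of the planned effect.
- Gap 0.8, correlation 0.3: 0.8 × 0.3 = 0.24, which is 0.24/0.70 = 34%.

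**False-positive rate with no true effect.** With 34 completers per group, the shift in the test statistic is bias × √17.

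- 0.15 × 4.12 = 0.62: P(Z > 1.34) + P(Z < −2.58) = 0.090 + 0.005, about 9.5%.
- 0.24 × 4.12 = 0.99: P(Z > 0.97) + P(Z < −2.95) = 0.166 + 0.002, about 16.8%.

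**Simulation 1.** Random intercept and slope, 50 per group, no true programme effect, correlation with change 0.3, 300 to 600 replicates. Mean group-by-time estimate in SD of change:

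| Scenario | No covariate | Main effect | Main effect + covariate-by-time |
|---|---|---|---|
| Gap 0.5, complete data | 0.151 | 0.151 | 0.004 |
| Gap 0.5, 30% dropout | 0.154 | 0.155 | 0.012 |
| Gap 0.8, 30% dropout | 0.242 | 0.242 | 0.003 |

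Rejection rates in the two dropout rows were 8.3%, 9.0% and 3.8%, then 17.5%, 17.5% and 5.0%, in line with the hand calculation.

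**Simulation 2, independent.** Random intercept, N = 100, gap 0.8 SD, 120 to 150 replicates. The covariate shifts 24-month change by 0.5 outcome units per SD, a deliberately strong setting in which 0.8 × 0.5 = 0.40 is expected.

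| Scenario | No covariate | Main effect | Main effect + covariate-by-time |
|---|---|---|---|
| Complete data | 0.399 | 0.399 | 0.004 |
| 30% dropout at random | 0.394 | 0.394 | −0.005 |
| Dropout dependent on the covariate | 0.367 | 0.381 | 0.005 |

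With complete data the first two estimates agreed to six decimals in every replicate. With dropout they differed by 0.013 to 0.025 on average and by 0.08 at most. When the covariate did not affect change, all three models centred near zero (complete data: −0.003, −0.003, 0.000).

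Rejection rates in the three rows were 46%/46%/10%, 38%/40%/6% and 35%/37%/5%. The 10% comes from 150 replicates (Monte Carlo standard error √(0.05 × 0.95/150) = 1.8 points). That model is correctly specified for the simulated data, so I read the 10% as simulation noise, not as a cost of the covariate-by-time term.

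**The case against.** The strongest objection is that the article does not commit to main effects. It neither states nor excludes covariate-by-time terms, and the sentence on comparing slopes does not list every term in the model. Change is described as the modelled quantity, so controlling for a variable could mean letting it predict change. Mplus, which the article names alongside SAS, can regress a slope on covariates. The covariate list is given as examples, and a fuller plan may settle the matter. All of this stands, and it makes the point conditional on the usual reading. It does not remove the point: the article fixes the contrast and the form of adjustment, and an analyst who follows the plain wording would obtain an adjustment that does not reach the contrast.

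Three stronger readings are tempting, and the article does not support them.

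- *The comparison is in effect unadjusted.* Too strong. A slope contrast already removes constant level differences, and main effects can help where dropout depends on the covariates. What is left is measured confounding of change.
- *Covariate control is the only protection.* The article also argues that the two sites serve similar women, and the Discussion promises further approaches. Those approaches are unnamed, so they can be neither credited nor ruled out.
- *The planned result is biased by a known amount.* The gap and the correlation are assumed, and the range includes zero.

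It is also fair that covariate-by-time terms are one remedy among several. Weighting on the baseline covariates could serve the same purpose.

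**Conclusion.** The point holds in conditional form. If the baseline variables enter as main effects, which is the ordinary meaning of the text, the group-by-time estimate is exactly the same with or without them in complete data and nearly the same at the planned attrition. Measured confounders of change are then unadjusted in research questions 1a and 1b.

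The bias is zero if the covariates do not affect change. It is about 0.15 to 0.24 SD of change (21% to 34% of the planned d = 0.70) under a gap of 0.5 to 0.8 SD and a correlation of 0.3, with false-positive rates of roughly 9% to 17% against a nominal 5%. The algebra is certain; these sizes are illustrations for a single covariate. The matter deserves settling before analysis because it concerns the primary contrast of a study with acknowledged selection bias that means to attribute the difference to BTC.

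**What to change.** In the Statistical analysis section, name a short, pre-specified set of baseline confounders. State that each enters the models for research questions 1a and 1b both as a main effect and as a covariate-by-time term. The group-by-time estimate is then the programme difference in change at equal covariate values. Report the model without the covariate-by-time terms as a sensitivity analysis.

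The change uses data already to be collected. It costs one extra parameter per covariate (more if time is categorical) and a slightly wider interval; with about 34 completers per group, that is the reason to keep the set short. It deals with measured confounders only. Unmeasured differences between the sites remain, and the attribution statement in the Discussion should be read with that limit.

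### The primary mixed model does not use time in treatment, which may drive both loss by 24 months and child outcome, so the BTC effect could be overstated by roughly 2–15%

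*Protocol article*

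**What the plan says.** - **Primary model (Statistical analysis, question 1a).** Linear mixed models describe change in each primary outcome from baseline to 24 months. The group slopes are compared by an interaction, with control for demographic variables such as maternal age, socioeconomic status and maternal ACEs. On missing data: "Linear mixed models can accommodate participants with missing observations". Question 1b follows a similar approach.
- **Engagement (Data collection).** Time in the programmes averages 18 months, with a range of 4 to 71, and "some mothers will remain in the program for the duration of the study while others will not". Leavers are offered a return visit, a telephone interview or a neutral meeting place.
- **Dose and outcome.** Question 2a (Objective) asks what mediates the association of treatment dose with infant mental health. The question 2 analysis is run in BTC "with time in treatment as the independent variable and infant mental health outcomes at 24 months as the dependent variable".
- **Attrition (Sample size and power calculations).** "Assuming ~ 30% participant attrition [25], a sample size of" 68 mothers with complete data is expected from about 98 enrolled.
- **Data at hand (Data collection).** The community-based researchers extract "treatments accessed, and treatment duration via retrospective file review".

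**The concern.** That a mixed model can be fitted to incomplete records is true. Whether the resulting contrast is unbiased for all enrolled mothers is a separate matter. It requires that, among mothers alike in demographics and observed scores, those lost would have had the same 24-month outcome as those seen.

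The protocol's own premises make this doubtful. It treats time in treatment as related to child outcome. Mean engagement is shorter than the 24-month endpoint. Mothers still in services are assessed on site, while leavers have to be brought back or reached elsewhere, so they are plausibly the harder group to retain. Time in treatment would then be a common cause of loss and outcome that the primary model leaves out.

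At stake is the main BTC-versus-MWCHC estimate. The social return on investment (question 3) builds on the question 1 evidence, so an overstated effect would also enter the benefit side of the benefit-cost ratio.

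**Working it through.** **1. The plan's own figure.** Inputs from Sample size and power calculations: "between-group effect size of Cohen’s d = 0.70", "assuming a two-sided two-sample t-test with un-pooled variance", alpha 0.05, 34 completers per group. The noncentral t distribution gives 81.2% power (stated: 81.1%). Inflation for loss: 34 / (1 − 0.30) = 48.6, so 49 per group and N = 98, as stated. The sizing reproduces.

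**2. Upper limit by algebra.** Suppose all of the 30% lost are early leavers, their observed scores carry no warning, and they gain a fraction k of the retained BTC mothers' benefit (k is assumed). With an estimate of 0.70:

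all-mothers effect = 0.70 × (0.70 + 0.30k); overstatement = 0.70 × 0.30 × (1 − k)

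| k | all-mothers effect | overstatement | share of 0.70 |
|---|---|---|---|
| 1 | 0.70 | 0 | 0% |
| 0.75 | 0.65 | 0.05 | 8% |
| 0.5 | 0.595 | 0.105 | 15% |
| 0 | 0.49 | 0.21 | 30% |

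This is a limit, because the mixed model conditions on each mother's own observed scores.

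**3. Letting the model use 12-month scores.** Assumptions, none of them in the protocol except as noted:
- Engagement is 4 months plus an exponential with mean 14 (matching the stated minimum and mean).
- The correlation of 12- and 24-month scores is 0.5.
- Overall loss is 30% (as stated).
- The true all-mothers BTC effect is 0.70, with half or all of it proportional to months received.
- MWCHC has no duration-related benefit.

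Under this distribution 1 − exp(−8/14) = 44% leave before 12 months. To keep overall loss at 30%, the loss among the others is (0.30 − 0.435q) / 0.565, where q is the loss among those leaving before 12 months.

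| q | loss in the others | overstatement, % of 0.70 | in d units |
|---|---|---|---|
| 30% | 30% | none | 0 |
| 40% | 22% | 2.3–4.8% | 0.016–0.034 |
| 50% | 15% | 4.5–9.8% | 0.032–0.069 |
| 60% | 7% | 7.2–14.7% | 0.050–0.103 |

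The lower end of each range has half the benefit proportional to months, the upper end all of it.

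**4. How far 12-month data help.** Take the extreme case in which every lost mother is an early leaver with no benefit at either visit, but all have a 12-month score. The true effect is 0.49. The estimate is 0.66 to 0.67 with unstructured means and 0.63 with a linear slope, against 0.70 with no 12-month scores. The bias shrinks but does not disappear.

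**5. Cases with no bias.**
- Loss unrelated to leaving: true 0.49, estimate 0.48.
- Leaving costs the same benefit in both programmes: true 0.71, estimate 0.69.

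Both differences are within simulation error (standard error 0.026).

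**6. With duration as an auxiliary variable.** In a further simulation mothers leaving before 24 months were up to 1000 times as likely to be lost. The mixed-model bias reached 9.2%; adding months in treatment as an auxiliary variable brought it to within 0.2% of zero. With 50 per group the standard deviation of the estimate rose from 0.241 to 0.247 in one case (0.247/0.241 = 1.02) and from 0.233 to 0.254 in the worst (1.09).

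**The case against.** **Only a condensed article is shown.** Multiple imputation details and sensitivity analyses commonly sit in an analysis plan. This stands for sensitivity analyses: that none is described here is no finding. It does not dispose of the point, because the article fixes the primary model and gives the model's tolerance of missing records as its answer to attrition, while naming elsewhere a collected variable that would serve better.

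**Leaving is not loss.** Leavers are offered three ways to take part, consent to further contact is sought at recruitment, and vouchers rise from $50 to $75 to $100 partly to reduce attrition and are paid to mothers no longer in services. Nothing says that leavers make up the 30%. This stands and makes the bias conditional.

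**The direction is not automatic.** A reader might infer that the result is biased towards BTC whenever the lost BTC mothers stayed for less time. The documents do not support that. MWCHC mothers leave too, and the Discussion says that MWCHC services benefit children indirectly. Only a difference between programmes in duration-related benefit, or in loss, produces a net bias. That most infant mental health components are offered only at BTC (Table 1) makes such a difference plausible, not certain. Leaving could also follow improvement, which would weaken or reverse the bias.

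**The size is modest.** With 34 per group the standard error of d is about sqrt(2/34) = 0.24, so even the largest value in step 3, 0.103, is under half a standard error. This stands. The error is nonetheless systematic, and the means to reduce it are already collected.

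**Conclusion.** The point holds as a conditional one. The primary model relies on loss being unrelated to the unseen outcome given demographics and observed scores, and the protocol's own premises give reason to doubt that. If early leavers are lost more often and duration-related benefit is larger at BTC, the BTC effect is overstated by roughly 2–15% of d = 0.70 over the loss patterns examined. The protocol does not give loss by engagement, so this is a range that rests on the assumptions in step 3.

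Two stronger readings should be avoided. One is that the model gives lost mothers the same expected course as retained mothers in their programme. It does not, because it conditions on their observed scores, so the 8%, 15% and 30% of step 2 are upper limits. The other is that the plan's result will be biased. Nothing in the document establishes that, and the bias is zero in the two cases of step 5.

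The change is worth making because it is cheap and is tied to a variable that the protocol already links to outcome.

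**What to change.** For questions 1a and 1b, handle missing 12- and 24-month scores with two auxiliary variables: treatment duration up to each visit, and whether the mother was still in services or had left at that visit. Duration is already taken from the clinical files, and status follows from it, so both can be known for mothers who miss a visit. Either of two routes serves:
- multiple imputation done separately within BTC and MWCHC, with the baseline covariates and observed scores; or
- full-information likelihood with auxiliary variables in Mplus, which the protocol already names.

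Then fit the planned mixed model. Do not add time in treatment as a covariate: it is measured after baseline, and adjusting for it would change the question from the effect in all enrolled mothers.

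Cost: analysis wording and some programming, with no new data, visits or participants. Intervals may be slightly wider (about 2% in one simulated case and 9% in the worst), and the estimated BTC effect may be smaller. The method still assumes that loss is unrelated to outcome once duration is taken into account, and it needs some early leavers to be observed in each programme.
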